### Provisions for post-trial care

Ancillary treatment is not planned during the intervention period due to confounding influence. In case of severe mental health conditions (e.g., suicidal ideation), requiring immediate standard of care treatment (inpatient, psychotherapeutic), the patient will be transferred to treatment by the established infrastructure. In the same manner, post-trial care is provided in case of severe disease aggravation by the end of trial participation.

If a participant withdraws prematurely from the study, their reasons, circumstances, and final status will be documented where possible. If the patient does not withdraw the consent for further follow‐up, he/she will be followed‐up as planned. If any harm arises from participation, such as an epileptic seizure or headache, standard treatment for the symptoms will be provided at the hospital immediately.

No post-treatment taper phase is included within the present protocol, since the trial was designed to closely mirror the FDA-approved iTBS standard and the addition of taper sessions was not feasible within the capacity of a pilot study. However, outside the study, participants have the opportunity to receive further treatment in our Day Clinic for Brain Stimulation, where standard iTBS is routinely available as part of clinical care. This option does not constitute a study-related provision but reflects the regular treatment pathways available to all patients. This ensures that participants who require continuation therapy can receive it under standard clinical conditions.. Future confirmatory trials will address this issue by incorporating taper phases or maintenance protocols, thereby providing a more complete picture of how oscillation-synchronized TBS can be implemented in clinical practice.

## Outcomes

### Primary endpoint

The primary outcome measure of the study is the change in the Montgomery-Åsberg Depression Rating Scale (MADRS) after the last interventional session (4 weeks after baseline) compared to at the baseline measurement before the first treatment session. The Montgomery-Åsberg Depression Rating Scale is a questionnaire for external assessment of the severity of a depressive syndrome. The questionnaire consists of 10 questions that are rated on a 7-point scale from 0 to 6. The total score ranges from 0 (best outcome) to 60 (worst outcome) points. The questionnaire is considered gold standard in the assessment of depressive symptoms [46].

### Secondary endpoints

Change in MADRS 4 weeks after the last treatment session vs. measurement before the first treatment session.Response rate after the last treatment versus baseline measurement before the first treatment session. A response is defined as a 50% reduction in the MADRS score from baseline [47].Remission rate after the last treatment versus baseline. measurement before the first treatment session. Remission is defined by a MADRS score below 8 points [47].Change in HDRS-17 (Hamilton Depression Rating Scale-17) after the last treatment session vs. measurement before the first treatment session. The HDRS-17 rates the severity of depressive symptoms in patients based on 17 structured interview questions performed by a clinican. A score of 0–7 is considered to be normal while a score of 20 or higher indicates at least moderate severity [48].Change in BDI-II (Beck Depression Inventory-II) after the last treatment session vs. measurement before the first treatment session. The BDI-II is a 21-question multiple-choice self-report inventory and represents the most widely used psychometric test for assessing the severity of depression in patients. More than 29 points reflect high severity of depressive symptoms, whereas a score below 13 points reflects mild depressive symptoms [49] [50].Change in IDS-30 (Inventory of depressive symptoms-30) after the last treatment session vs. measurement before the first treatment session. The IDS-30 is considered equivalent to or superior to the standard Hamilton Depression Scale (HDRS) and Beck Depression Inventory (BDI) tests. The scores ranges from 0 to 84 points. Patients who score from 39 upwards are considered severely depressed [51].

### Exploratory end points

Exploratory outcome measures will be changes in resting-state EEG immediately after and 4 weeks after the last treatment session vs. a baseline measurement before the first treatment session. In particular, the power spectrum density function derived from the 5-channel AFF1h-centered Hjorth montage and functional connectivity from the stimulated AFF1h electrode to all other EEG electrodes, using the weighted phase lag index in the theta frequency band, will be explored.

### Participant timeline

The TMS intervention duration for each subject is 4 weeks (20 sessions, 5 sessions per week). The maximum study duration including screening, MRI scan, TMS intervention and a 4-weeks follow-up measurement for each subject will be 3 months. The time course of events can be seen in Table 1.

**Table 1 Tab1:**
[figure not shown]
Study Visits with clinical assessment timeline and diagnostic scores per treatment phase

There will be three types of study visits which will be described in detail below:Screening VisitAssessment VisitTherapy Visit

#### Screening visit

After having obtained written informed consent the screening visit consists of checking for inclusion/exclusion criteria incl. MRI safety checklists, physical and psychiatric examination and scheduling the MRI scan.

The screening visit also includes a resting-state EEG measurement (32 channels, 5 min, eyes open). This EEG is analyzed for spectral power in the theta range (4–8 Hz). A clear theta peak must be present to qualify for study participation, as this feature is necessary for the functioning of the real-time EEG-triggered stimulation algorithm. The spectral analysis is presented graphically, and eligibility based on this criterion is confirmed by senior investigators.

A second brief screening visit will be scheduled within 3 days prior to the first scheduled therapy visit to ensure that the patient still fulfills the inclusion criteria. An MRI measurement will be scheduled between the two screening visits. The stimulation sites will be marked. Resting Motor Threshold determination and randomization will also be performed in this visit.

#### Assessment visits

Each patient will receive four evaluations: a pre-evaluation (T1; prior to the first intervention), an intermediate evaluation (T10; after the 10th intervention), a post-evaluation (T20; after the final intervention), and a follow-up evaluation (P2) conducted four weeks after the last intervention.

These assessments will include clinical evaluations (MADRS, HDRS-17), self-report questionnaires (BDI-II, IDS-30), a 32-channel EEG, and TMS measures of motor cortical excitability (RMT). The randomization is performed between the pre-evaluation and the first treatment session.

#### Therapy visit

A 5-channel EEG cap with an AFF1h-centered Hjorth montage (AFF1h AFp1, AFF2h, FFC1h, AFF5h) with active electrodes using ActiCHamp (BrainProducts GmbH, Gilching, Germany) will be prepared, followed by registration of the MRI-based TMS-navigator. In both conditions MRI-navigated TMS with 600 pulses per session will be applied to the prefrontal cortex. The intervention protocol (EEG-synchronized rTMS over left DMPFC or standard iTBS over left DLPFC) depends on the randomization. The patients will not be informed about their assignment to the experimental or control protocol.

At the start of each study visit, patients will be asked about changes in medication. The patient is asked about the occurrence of any adverse events at the end of each therapy visit and again at each subsequent study visit to account for adverse events that may have occurred between sessions. In the case of adverse events, any event will be documented in the case report form, a study physician will be consulted and feedback is given to the principal investigator and the sponsor. The principal investigator decides on the severity of the adverse event and further study participation in consultation with the patient. In case of changes in the medication, the patient must be excluded from further participation.

### Participants and recruitment

Thirty patients with MDD as diagnosed by the Diagnostic and Statistical Manual of Mental Disorders (DSM-5) in the age range of 18–65 years will be included. Potential candidates will be addressed by contacting local patient advocacy/support groups, local psychiatrists/general practitioners, as well as information via clinic website, social media, newsletters, local newspapers, or advertisement in public transportation.

Both men and women are eligible. Gender and age distribution will be documented and reported in the trial results. While the study is not powered to detect gender-specific effects, exploratory analyses will be undertaken to investigate potential trends in treatment response by gender. These analyses may provide preliminary data for subsequent pooled or confirmatory trials.

## Methods: assignment of interventions

### Allocation, sequence generation and implementation

Participants will be randomly allocated to either the control or experimental group in a 1:1 ratio based on a computer-generated randomization list provided by The Institute of Clinical Epidemiology and Applied Biostatistics at the University of Tübingen (IKEaB). The randomization will be provided in envelopes that indicate the assigned stimulation protocol. The operator is responsible for implementing the assigned treatment while ensuring the patient remains blinded.

### Blinding

Assessments of the clinical endpoints will be conducted by an assessor blind to treatment allocation. Participants and assessor will be blinded to the allocation. The therapy provider cannot be blinded to allocation due to the nature of the intervention, but is encouraged not to disclose the allocation status to the patient or the assessor.

Procedure for unblinding if needed:

To maintain the overall quality and legitimacy of the clinical trial, unblinding should occur only in exceptional circumstances when knowledge of the actual treatment is absolutely essential for further management of the patient. Investigators are encouraged to discuss with the principal investigators if unblinding is necessary. If unblinding is necessary, the investigator should use the system for emergency unblinding. However, no scenario can yet be identified in which unblinding would be medically necessary. Given that both therapy arms include effective TMS and that the therapies do not differ medically in terms of their risk profile, in this study unblinding would not have a therapeutic consequence.

The Investigator is encouraged to maintain the blinding as far as possible. The actual allocation must not be disclosed to the patient and/or other study personnel including other site personnel, monitors, corporate sponsors or project office staff; nor is there any written or verbal disclosure of the code in any of the corresponding patient documents. The investigator reports all unblinding (with reason) to the data management department at the IKEAB (Institute for Clinical Epidemiology and applied Biostatistics, University Tübingen).

## Data collection, management and analyses

### Plans for assessment and collection of outcomes and data management

The informed consent process is documented and all the original signed documents will be part of the investigator’s site file and retained with it. One copy including the insurance policy of the trial will be handed to the patient. All procedures administered to the subjects on entry to the trial or at any time during the trial will be documented paper-based in a pseudonymous manner. At the end of each visit, the data will be entered into a paper-based CRF. The CRFs have been validated and approved by the IKEaB.

The investigator’s site file will be stored in the TMS study center of the University of Tübingen in accordance with the regulatory requirements of General Data Protection Regulation (GDPR) directives. Only authorized staff will have access to the data. All source data will be photocopied, pseudonymized and digitally stored on the secured storage area network (SAN) of the University Hospital Tübingen. Subjects’ files will be saved using codes in order to protect their privacy. Volume cloning ensures instantaneous data backup. Publication of data, e.g. in the form of a scientific oral presentation or publication will only contain anonymized data. MRI data will also only be saved in a pseudonymized way. Data will be entered in a database (www.koordobas.de) and checked for errors, consistency and completeness before submitting to the statistical analyses. All data will be stored for a minimum of 10 years to enable data reanalysis and sustained availability.

### Confidentiality

Data acquisition and storage is performed in accordance with the regulatory requirements of General Data Protection Regulation (GDPR) directives. CRFs or other data that might be photocopied for verification by authorized persons will be pseudonymized, i.e., they will not contain the name of the participants but only their unique identification code. The identification code consists of an abbreviation of the study acronym (BF2) plus the number of the participant. Published data (e.g., in form of scientific oral presentations or publications) will only contain anonymized data. Participants’ files will be saved using codes in order to protect their privacy.

### Plans for collection, laboratory evaluation and storage of biological specimens for genetic or molecular analysis in this trial/future use

Not applicable, no samples collected.

## Statistical methods

### Methods and analyses

All statistical analyses will be based on the Intention-to-Treat Population (ITT). The ITT includes all randomized patients with exception of patients who withdraw their informed consent for the analysis of their data during the study. Additionally, as per protocol analysis of main results will be provided, if ITT differs from PP by more than four patients.

The primary endpoint is the relative change (%) of MADRS between baseline and the last therapy session. The primary endpoint will be compared between the two study groups. The null-hypothesis is that there is equal relative change of MADRS in both groups. The alternative hypothesis is that the experimental group has a greater relative change of MADRS. For analysis of the primary endpoint variable a baseline adjusted analysis of covariance will be performed to test the null hypothesis against the alternative hypothesis. The test of the factor “treatment” will be based on a significance level of α = 0.05 one-sided. Effect size and 95%-confidence interval for effect size will be estimated. The rejection of the null hypothesis will be interpreted as justification to plan a confirmatory RCT. Additionally, a mixed model will be calculated including all measurements of MADRS with study arm and time as factors and the time vs treatment interaction as parameter of interest. In this analysis, screening and measurement before treatment at T1 will be pooled.

All secondary outcome measures will be compared and statistically assessed for descriptive purposes and not in a confirmatory sense. The aim of these analyses is explorative, not hypothesis testing or evidence for efficacy generating, and no attempt will be made to adjust the p-values of statistical tests of the secondary endpoints for multiple testing. If adequate, secondary endpoints will be compared and statistically assessed using t-tests for two groups or analysis of covariance techniques with baseline values as covariates in case of quantitative variables. Depending on distribution, non-parametric tests may be indicated. Dichotomous data will be compared and statistically assessed using Mantel–Haenszel chi-squared tests including relative risks and 95%-confidence intervals for relative risks and by using logistic regression models.

All variables included in the CRF are mandatory. The monitoring will assure quality of the assessments. Thus, missing values are to be expected only due to refusal by patients. Missing values will be simulated using multiple imputation. The percentage number of sessions (at most 20 = 100%) will be used as a covariate, this means, in patients with zero sessions, jump to reference will be applied. Zero % change, complete case and last observation carried forward analyses will be performed as sensitivity analyses.

Safety will be assessed by frequency tabulations and line listings, and exact 95% confidence intervals if adequate.

Descriptive analyses will include absolute and percentage frequencies for categorical variables, means, medians, standard deviations, quartiles and ranges for quantitative variables and medians, quartiles and ranges for ordinal variables.

No subgroup and no interim analyses are planned. There are no stopping rules to define. Due to the missing interim analyses there are no criteria for an early stop of the clinical trial. If a patient worsens during the treatment period this could be defined as an individual reason for an early drop out of the study.

Statistical analyses will be conducted by the Institute for Clinical Epidemiology and applied Biostastistics of the University of Tübingen, once database is declared closed. In this study protocol the outline of the planned analyses are given. Before starting the final analysis, a detailed statistical analysis plan will be written and signed by the responsible statistician and the coordinating investigator. If any major deviations in the SAP from the original study protocol are necessary, the reason for that will be given in detail. A protocol amendment will be adequate for major deviations (e.g., change of primary endpoint, sample size). The final SAP will be documented in the final biometrical report. The biometrical report will be written by the responsible statistician and should include the complete statistical analysis.

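### The continuous secondary endpoints may be analysed by an unadjusted t-test although each scale has a baseline value; naming baseline-adjusted ANCOVA would usually give tighter estimates at almost no cost

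*Protocol article*

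**What the plan says.** All of the following is in the protocol article.

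- **Primary endpoint** (Methods and analyses). One method is fixed: "For analysis of the primary endpoint variable a baseline adjusted analysis of covariance will be performed".
- **Quantitative secondary endpoints** (same section). The sentence opens "If adequate, secondary endpoints will be compared and statistically assessed" and continues "using t-tests for two groups or analysis of covariance techniques with baseline values as covariates in case of quantitative variables". It is followed by "Depending on distribution, non-parametric tests may be indicated". The section gives no order of preference between the t-test and ANCOVA.
- **Status of these endpoints** (same section). "All secondary outcome measures will be compared and statistically assessed for descriptive purposes and not in a confirmatory sense".
- **Definitions** (Secondary endpoints). The continuous ones are changes from before the first session, for example "Change in MADRS 4 weeks after the last treatment session vs. measurement before the first treatment session". HDRS-17, BDI-II and IDS-30 are defined the same way at the end of treatment.
- **Baselines** (Assessment visits). Of the four evaluations, the first of which (T1) precedes treatment, the text says "These assessments will include clinical evaluations (MADRS, HDRS-17), self-report questionnaires (BDI-II, IDS-30" and so on. Every continuous secondary endpoint therefore has its own baseline value.
- **Later detail** (Methods and analyses). "Before starting the final analysis, a detailed statistical analysis plan will be written and signed".

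**The concern.** The plan adjusts the primary endpoint for baseline but names an unadjusted comparison as an equal alternative for the continuous secondary endpoints, with the same kind of baseline data available. Because these endpoints are defined as changes, the t-test would most naturally be run on the change score. That test does use the baseline, but with a fixed weight of one rather than the weight the data support. It is therefore generally less precise than ANCOVA, and with about 14 patients per arm it leaves part of any chance difference at baseline in the estimate.

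What is at stake is the quality of the descriptive estimates. The Background and rationale section says the pilot is meant to supply effect-size estimates for planning a definitive trial, and the usefulness of a descriptive estimate lies largely in its precision.

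**Working it through.** **The plan's own figure.** No figure is given for the secondary endpoints. The Sample size section gives 13.6 per group for the primary endpoint (difference 20, SD 17.9, two-sided α = 0.05, 80% power). An exact noncentral-t calculation gives 13.60 per group, and power 0.812 at 14 per group. The stated figure reproduces. I use its 28 assessable patients, 14 per arm.

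**Inputs that are not in the documents.** These are r, the correlation between baseline and endpoint score (assumed 0.3 to 0.6), and k = SD(baseline)/SD(endpoint) (assumed 1, then varied). The SD of 17.9 refers to percentage improvement and fixes neither. I read change as the arithmetic difference.

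**Variance ratio.** With endpoint SD σ, the variance of a change score within an arm is σ²(1 + k² − 2rk). The ANCOVA residual variance is σ²(1 − r²). So

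R = (1 − r²) / (1 + k² − 2rk).

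For k = 1 this is (1 − r²)/(2(1 − r)) = (1 + r)/2. Estimating the slope costs a factor of about 1 + 1/(N − 4) = 1 + 1/24 = 1.042 at N = 28.

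**Equal SDs (k = 1).**

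| r | (1 + r)/2 | × 1.042 | Relative CI width (square root) | 28 ÷ ratio |
|---|---|---|---|---|
| 0.3 | 0.65 | 0.68 | 0.82 | about 41 |
| 0.6 | 0.80 | 0.83 | 0.91 | about 34 |

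Intervals are about 18% narrower at r = 0.3 and about 9% narrower at r = 0.6. The last column is the number of patients a change-score t-test would need to match ANCOVA on 28. The width ignores the change from 26 to 25 residual degrees of freedom, which is negligible.

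**Unequal SDs.** R = 1 when k = r, so the gain can vanish. At k = 0.6 and r = 0.5, R = 0.75/(1 + 0.36 − 0.60) = 0.75/0.76 = 0.99. With the finite-sample factor it is 0.99 × 1.042 = 1.03, slightly in favour of the t-test. A smaller baseline SD is plausible for MADRS because entry requires a score of at least 20, but no score SDs are given.

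**Chance imbalance.** With 14 per arm, the standard error of the baseline difference is √(2/14) = 0.38 SD, and a difference at least that large in either direction occurs in about one trial in three. With equal SDs, a change-score comparison carries (1 − r) of it into the estimate: at r = 0.5, 0.5 × 0.38 = 0.19 SD.

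**The case against.** The strongest reply is that this is detail for the analysis plan. The article calls itself an outline, promises a signed plan before the final analysis, and already lists ANCOVA among the options. The secondary endpoints are declared descriptive, and the decision to plan a confirmatory trial rests on the primary test alone. Follow-up MADRS also enters the mixed model that uses all MADRS measurements. All of this stands, and it makes the point minor. It does not remove it: the article expressly permits the weaker method, and an analysis plan that kept the t-test would comply with it.

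The reply is also right that the gain depends on the SDs at the two times, and the result is stated with that condition.

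Three stronger readings are tempting and are not supported:

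- **The choice between t-test and ANCOVA waits until the data are seen.** The article does not say so, and the promised plan may settle it. Only the switch to a non-parametric test is tied to the distribution. Picking the smallest p-value among a change-score t-test, ANCOVA and a Mann-Whitney test would raise a nominal 5% error to about 7% to 9% per endpoint in simulation, but nothing in the article describes such picking.
- **Every secondary interval is widened.** Response and remission are dichotomous and have their own methods. Precision on the continuous scales is lost only if an unadjusted method is actually used.
- **Effect sizes would not be comparable across scales.** Under randomisation, a change-score t-test and ANCOVA estimate the same mean difference. They differ in precision, not in target.

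**Conclusion.** The point holds as a minor one. The article allows an unadjusted t-test for four continuous secondary endpoints whose baselines are collected and which could be handled like the primary endpoint. If that option is used on change scores, ANCOVA would generally have been more precise: about 0.68 to 0.83 of the variance, or intervals about 9% to 18% narrower, at N = 28. This rests on equal SDs at baseline and endpoint and a correlation of 0.3 to 0.6, neither of which the documents give. If the baseline SD is much smaller than the endpoint SD, the gain shrinks towards nothing.

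A reader might infer that the secondary results are open to data-driven selection or that the trial's main conclusion is weakened. The documents support neither: a signed plan is due before analysis, the endpoints are descriptive, and the primary analysis is already baseline-adjusted.

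**What to change.** In Methods and analyses, replace the choice between t-test and ANCOVA with one main method for every continuous secondary endpoint. This is ANCOVA of the end-of-treatment value (the follow-up value for follow-up MADRS), with arm and that scale's own T1 value as covariate, reported as the adjusted mean difference with 95% CI. Drop the unadjusted t-test. Non-parametric tests can remain as a supporting analysis where the distribution calls for them.

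The change is one sentence. It needs no new data or visits and costs one degree of freedom per model.

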### Criteria for discontinuing or modifying allocated interventions

If the stimulation is not tolerated by the patient, the stimulus intensity will be first adjusted to the highest tolerated intensity and then gradually adjusted to the required intensity over max. 3 sessions. If the patient cannot become acquainted with the treatment conditions (e.g., stimulus intensity) within three sessions, additional participation is not feasible. Withdrawal from the study is also required if the subject misses more than 4 planned treatment sessions. In the case of up to 4 missed planned treatment sessions, the missed sessions will be offered at the end of the intervention period, so that each enrolled patient will receive 20 sessions. However, we strive to keep the number of treatment cancellations and postponements to a minimum. Patients who withdraw from the study will be included in the primary statistical analysis (cf. section “Statistical Methods”).

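### The missing-data plan expects values to be lost only through refusal, but the protocol also allows exit for worsening, schedules no MADRS at stopping and leaves rating after withdrawal unclear

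*Protocol article*

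**What the plan says.** **Premise and method (Methods and analyses).** The article expects that "missing values are to be expected only due to refusal by patients". It continues: "Missing values will be simulated using multiple imputation". The rule for the imputation model reads: "The percentage number of sessions (at most 20 = 100%) will be used as a covariate, this means, in patients with zero sessions, jump to reference". Three checks follow: "Zero % change, complete case and last observation carried forward analyses will be performed as sensitivity analyses".

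**Worsening (same section).** "If a patient worsens during the treatment period this could be defined as an individual reason for an early drop out of the study". No scale, threshold or decision-maker is given.

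**Other exits that are not refusal.**
- Criteria for discontinuing or modifying allocated interventions: "Withdrawal from the study is also required if the subject misses more than 4 planned treatment sessions". Patients who cannot get used to the stimulation within three sessions also cannot continue.
- Provisions for post-trial care: in severe conditions "requiring immediate standard of care treatment (inpatient, psychotherapeutic), the patient will be transferred to treatment".
- Eligibility criteria and Therapy visit: a change of medication ends participation.

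**What happens after withdrawal.** The discontinuation section keeps withdrawn patients in the primary analysis. Provisions for post-trial care has them followed up on schedule unless they withdraw consent to this, and records their final status where possible. It names neither a MADRS nor the blinded rater for that record.

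**Rating schedule (Assessment visits).** Clinical ratings are made before treatment, after session 10 (T10), after the final session (T20) and four weeks later (P2). None is tied to early stopping.

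**The concern.** Exit because of worsening depends on the outcome being measured. If the outcome of such a patient is then missing, an imputation model that does not know why the patient left will tend to supply a value resembling those of patients who stayed. The refusal-only premise hides this, because it implies that the protocol itself produces no missing values.

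The stake is the primary comparison. The article treats rejection of the null hypothesis as justification for planning a confirmatory trial, and with 14 assessable patients per arm a single patient carries one fourteenth of an arm mean. The rating is also hard to repair afterwards: recruitment is under way, and a MADRS not taken at stopping cannot be recreated by a later analysis plan.

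**Working it through.** **1. Does the refusal-only premise agree with the rest of the protocol?** No. Worsening, intolerance, more than four missed sessions, transfer to other care and medication change are all exits that the protocol allows or requires.

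**2. Does follow-up after withdrawal close the gap?** Only if it takes place. Provisions for post-trial care continues follow-up with consent. Eligibility criteria, the discontinuation section and Therapy visit say that participation is not possible, not feasible or must end, and the worsening sentence speaks of leaving the study, not of stopping treatment. The reader cannot tell which rule governs the week-4 MADRS.

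**3. What is known about a patient who stops at session 7 and is not rated later?** Only pre-treatment scores. Exposure is 7/20 = 35%. Up to four missed sessions are made up so that each patient receives 20, and those missing more are withdrawn. Patients with an observed outcome therefore sit at or near 100%. Unless withdrawn patients are in fact rated, the covariate varies little where outcomes are seen, so the data say little about what 35% implies. Jump to reference is stated for zero sessions only.

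**4. Size for one such exit.** From Sample size: mean improvement 48% (control) and 68% (experimental), SD 17.9, target difference 20 points, 28 assessable, so 14 per arm. (The stated 13.6 per group for 80% power with a two-sided t-test reproduces as 13.60.) Assumptions not in the documents: true change -10%, and imputation near an arm mean.

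Shift in arm mean = (imputed value - true value) / n

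| Handling | n = 14 | n = 17 (half of 34 randomised) |
|---|---|---|
| Imputed at 48% | (48 + 10)/14 = 4.1 | 58/17 = 3.4 |
| Imputed at 68% | (68 + 10)/14 = 5.6 | 78/17 = 4.6 |
| Zero change, or LOCF before T10 | (0 + 10)/14 = 0.7 | 10/17 = 0.6 |

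Two such exits in one arm of 14 double this: 8.3 to 11.1 points by imputation, 1.4 under zero change. After T10, LOCF carries the T10 score and can show worsening.

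**5. How often?** Under the article's own mean and SD with a normal distribution, P(change < 0) = Φ(-48/17.9) = 0.37% in control and Φ(-68/17.9) = 0.007% in the experimental arm, or about 0.06 patients among 17 controls. With an assumed SD of 30 to 40, it is 5.5% to 11.5% in control and 1.2% to 4.5% in the experimental arm.

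**6. Effect on the test.** Simulation: 20,000 runs, 17 per arm, one-sided α = 0.05, no true mean difference, worsened patients averaging -20%. Complete cases stand in for imputation that ignores worsening.

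| Worsened exits (experimental v control) | Complete-case bias, rejection | Zero-change bias, rejection |
|---|---|---|
| 2 v 0 | +9.1 points, 41% | +2.4 points, 3.5% |
| 2 v 2 | none, about 5% | none, about 1% |

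**The case against.** Much of the defence is sound. A reader might infer four stronger things that the article does not support.

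- *That worsened patients are removed.* They stay in the primary analysis and are followed up if they consent. Only the complete-case analysis drops them.
- *That they are imputed as if fully treated.* The percentage of sessions is a covariate. How far it helps depends on step 3, and the result could lie below the arm means used in step 4.
- *That no outcome is ever set below zero change, or that no listed analysis would reveal a problem.* LOCF can carry a worse T10 score, and imputed values are not said to be bounded. A gap of the size in step 4 between the imputed and zero-change results would itself be a signal.
- *That an unblinded provider decides who leaves.* The Blinding section says the provider knows the arm, but nothing gives the provider this decision. Therapy visit leaves continuation after an adverse event to the principal investigator with the patient.

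It can also be said that the refusal sentence concerns data collection, and that it is nearly true if withdrawers are rated. That holds only if follow-up prevails over the passages that end participation, which is what needs settling. The additional mixed model does not help a patient with no post-treatment rating.

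Finally, the detail of the imputation model properly belongs in the analysis plan promised in the article. The schedule of ratings does not: it must be fixed while patients are being treated.

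**Conclusion.** The concern holds in a limited form. The refusal-only premise contradicts the protocol's own exits, the rules on rating after withdrawal conflict, and no MADRS is scheduled at stopping. An unrated worsening exit before T10 is therefore imputed without the reason for leaving, while zero change and LOCF treat that patient as unchanged rather than worse.

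The size is conditional: about 4 to 6 points in one arm's mean per unbalanced exit by imputation, and about 0.7 under zero change, given 14 per arm, a true change of -10% and imputation near the arm mean. Equal exits roughly cancel in the treatment difference, and under the Sample size assumptions worsening would be rare. This is a gap worth closing now, not evidence that the primary comparison is invalid.

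**What to change.** The clinical decision to stop stays as it is; the change is to data collection and analysis.

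1. Replace the refusal-only sentence with the protocol's own reasons for exit, recorded by arm. Reconcile Eligibility criteria, the discontinuation section, Therapy visit and the worsening sentence with Provisions for post-trial care, so that stopping treatment does not end outcome rating.
2. Have the existing blinded rater complete a MADRS at stopping and, with consent, at week 4 and P2. Use the exit rating in the imputation model.
3. Add one sensitivity analysis for worsening exits, either carrying the exit score forward or applying a delta adjustment.

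Cost: one extra rating in a few patients, some wording in the protocol and analysis plan, and possibly a less favourable estimate.
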